### Interventions

Participants will be outpatients diagnosed with PSD up to 12 months after the index event. Following baseline assessments, all participants will receive the active treatment - Maraviroc 300 mg once daily for 10 weeks in an open-label design. They will be followed for another 8 weeks after cessation of Maraviroc. The study intervention will be given as add-on therapy to the patient’s usual prescribed care (treatment as usual),thus all participants will continue their existing antidepressant treatment without change. All participants will be instructed to continue their usual treatment for the whole trial duration. Endpoints:

Primary Safety Endpoint: No serious treatment-emergent adverse events (TEAEs), no TEAEs leading to discontinuation.

Primary Efficacy Endpoint: The primary efficacy evaluation will be the MADRS total score as measured by the change from baseline (i.e., Day 1 pre-dose) to Week 10.

Secondary Endpoints: • Proportion of responders • Proportion of subjects in remission • Change from baseline to week 10 in subject-reported depressive symptoms using the QIDS-SR16. • Change from baseline to week 10 in severity of illness using the CGI-S and CGI-I. • Change from baseline to week 10 in severity of illness using the PGI-S and PGI-C. • Change from baseline to week 10 in anxiety symptoms, as measured by the GAD-7. • Change from baseline to week 10 in the SIS, ADL, and RNL scores.

Neuroimaging acquisition and processing A magnet resonance imaging (MRI) protocol will be performed before visit 1 and will consist of previously described pulse sequences ^36^. All axial slices will be prescribed on the same orientation, covering the whole brain, aligned along the fourth ventricle-orbitofrontal orientation. MRI analyses will include assessment of white matter (WM) hyperintensities, tissue segmentation and Brain atrophy measures as we have previously described^36^.

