# We plan to perform a proof-of-concept open label add-on clinical trial of 300 mg Maraviroc given once daily for 10 weeks in 10 patients with PSD. Depression scores over time will serve as outcome measures and each patient function will be compared before and after treatment with study drug, beyond current treatment with other anti-depressants, such that the efficacy will be analyzed only beyond the efficacy of current treatments. The study will consist of 3 phases: (1) screening, (2) open-label treatment (weeks 1-10), and (3) post-treatment follow-up (8 weeks). The primary objective will be safety and tolerability of Maraviroc 300 mg per day in subjects with PSD. If proved safe, we plan continued research to establish efficacy using different dosages of Maraviroc

Objectives

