**Characteristics of human subjects**

**Inclusion Criteria**

1. Men and women aged 50 to 86 years;
2. Able to fully comprehend and sign an informed consent form;
3. Diagnosis of stroke/TIA prior to study entrance and evidence of ischemic infarct and/or lacunar infarcts on MRI (defined as sharply demarcated hypointense lesions <20mm on T1-weighted images with corresponding hypointense lesions with hyperintense rim on FLAIR) and/or deep Cerebral Microbleeds (CMB) (defined as round hypointense lesions on T2-weighted gradient echo-images with a diameter < 10 mm in neuroimaging.
4. Meet Diagnostic and Statistical Manual of Mental Disorders – Fifth Edition (DSM-5) diagnostic criteria for major depressive episode that developed up to 12 months after the documented stroke/TIA.
5. Able to comply with scheduled visits, treatment plan, and other trial procedures;
6. Treatment with other antidepressants is allowed but subjects will be asked not to change their regular treatment regime during the trial.

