**Overview of Study Design**

This is a proof-of-concept, open-label, single center study conducted in 10 male and female adult subjects with PSD. Each subject will participate in 3 phases: (1) a screening phase of up to 1 week, (2) an open-label treatment phase of 10 weeks, and (3) an 8-week post-treatment (follow up) phase. The end of study will occur when the last subject in the trial completes his/her last study assessment.

Screening and Baseline assessments

After giving informed consent, subjects will be screened to determine eligibility for study participation. Note: Subjects who are not currently taking an antidepressant at screening are eligible to participate in this study (i.e., subjects may participate in the study whether or not they are taking an antidepressant). Subjects who are taking an antidepressant at the screening visit must have been receiving a stable dose (i.e., dose has been unchanged for at least 2 months before the screening visit) and will be guided to continue the antidepressant at the same dose during the treatment phase. All adverse events and special reporting situations, whether serious or non-serious, will be reported from the time a signed and dated informed consent form (ICF) is obtained until completion of the subject's last study-related procedure (which may include contact for follow-up of safety). If a subject withdraws before the end of the treatment phase for reasons other than withdrawal of consent, the early termination visit should be conducted at the time of discontinuation, followed by completion of the posttreatment phase. All subjects will self-administer the study medication.

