**Interventions:**

Our participants will be free of hepatic, as well as renal impairment. The recommendation from the FDA is to obtain liver function tests prior to starting the drug and again should symptoms such as rash or hepatitis occur. This rather rare adverse reaction tends to occur at about one month after starting the medication (in less than 4% on the drug or placebo), so the investigators will obtain a bilirubin and transaminases at the planned 1-month follow up.

Adverse events related to the medication assignment, to rehabilitation practice or to other causes will be adjudicated by the safety committee with input from the principal investigator.

Patients will be contacted weekly by phone to help maintain interest in the trial, assure use of the assigned medication, and ask about possible adverse reactions. The coordinator will obtain this information and provide the feedback using a standard script and checklist.

**Quality control and analysis:**  All patient records and specimens will be tracked in a manner consistent with Good Clinical Practice by a quality-controlled, auditable, and appropriately validated laboratory information management system, to ensure compliance with data confidentiality as well as adherence to authorized use of specimens as specified in this protocol and in the Informed Consent Form.

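### The primary safety endpoint is worded as a required result of zero events, and in 10 uncontrolled patients neither zero events nor a single event can show whether the drug is safe

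*Protocol*

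**What the plan says.** Under Endpoints, in the Interventions part of Methods, the protocol states: "Primary Safety Endpoint: No serious treatment-emergent adverse events (TEAEs), no TEAEs leading to discontinuation". It gives no tolerated count, acceptable rate or restriction by cause.

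The Design section names safety and tolerability as the primary objective and adds: "If proved safe, we plan continued research to establish efficacy using different dosages of Maraviroc".

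The setting is small and uncontrolled: "This is a proof-of-concept, open-label, single center study conducted in 10 male and female adult subjects with PSD". The age criterion is "Men and women aged 50 to 86 years", and participants must have had a stroke or TIA. Treatment is "Maraviroc 300 mg once daily for 10 weeks in an open-label design". On follow-up: "They will be followed for another 8 weeks after cessation of Maraviroc". Adverse events are collected from consent "until completion of the subject's last study-related procedure (which may include contact for follow-up of safety".

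The later Interventions section says that adverse events, whether linked to the medication, to rehabilitation or to something else, "will be adjudicated by the safety committee with input from the principal investigator". The endpoint does not use the result of that adjudication.

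Statistical Analysis, under its heading for the primary safety endpoint, provides for tables of adverse events, vital signs, laboratory values and examinations. It states no test and no threshold. The sample size text in Supplemental Methods does read zero events as an upper bound on a rate, but only for sexual dysfunction, weight gain and hyponatremia.

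**The concern.** An endpoint should name what is measured. This one names the hoped-for answer. Because the Design section makes the next step depend on safety having been proved, and no other criterion is given, the natural reading is that an absence of events is the proof.

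That reading can mislead in two ways. If no event occurs, the report may claim proven safety although quite high event rates remain compatible with the data. If one event occurs, for example an unrelated hospital admission in an elderly stroke patient, the primary endpoint as worded has not been met even though the drug may be harmless, and there is no control arm against which to judge it. At stake is what the trial can honestly conclude on its primary objective.

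**Working it through.** **Inputs from the protocol.** n = 10, single arm; endpoint met only with 0 affected participants; 10 weeks on treatment plus 8 weeks of follow-up, 18 weeks in all.

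**Input that must be assumed.** p, the per-participant probability of at least one serious TEAE or TEAE leading to discontinuation, any cause, over the counting window (10 to 18 weeks, depending on what counts as treatment-emergent). The protocol gives no such rate for post-stroke patients, so a range is shown.

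**The protocol's own zero-event figures.** The sample size equation is not visible in the text. The standard exact bound after 0 of n events, at one-sided confidence C, is 1 − (1 − C)^(1/n). At 90%:

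| n | Bound | Protocol states |
|---|---|---|
| 8 | 1 − 0.10^(1/8) = 0.250 | 0.25 |
| 9 | 1 − 0.10^(1/9) = 0.226 | 0.22 |
| 10 | 1 − 0.10^(1/10) = 0.206 | 0.31 |

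The first reproduces and the second is close. The third does not: 0.31 with n = 10 matches one-sided 97.5%, since 1 − 0.025^(1/10) = 0.308. That is a separate discrepancy and nothing below depends on it. It does show that the plan already treats zero events as a bound.

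**What zero events would show for the primary endpoint.**

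- One-sided 90% upper limit: 1 − 0.10^(1/10) = 20.6%.
- Exact two-sided 95% upper limit: 1 − 0.025^(1/10) = 30.8%.

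For comparison, 1 of 10 gives an exact two-sided 95% interval of 0.3% to 44.5%. The intervals for 0 and 1 event overlap almost entirely, so the line between meeting and missing the endpoint separates results that carry nearly the same information.

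**How often each outcome occurs.** P(0 events) = (1 − p)^10, and P(at least 1) = 1 − (1 − p)^10.

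| Assumed p | P(0 of 10) | P(at least 1) |
|---|---|---|
| 2% | 81.7% | 18.3% |
| 5% | 59.9% | 40.1% |
| 10% | 34.9% | 65.1% |
| 20% | 10.7% | 89.3% |

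If p is purely background, the last column is the chance that a harmless drug misses the endpoint. It passes 50% only when p exceeds 1 − 0.5^(1/10) = 6.7%.

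**The case against.** The best reply is that no pass/fail rule has been written. Statistical Analysis is purely descriptive, and the sentence in Design is a loose remark about future plans that does not cite the endpoint or say that one event ends the programme. This stands in part: a reader might infer a formal test with a stated consequence, and the document contains none. But the endpoint still specifies the required result, Design still makes further research conditional on proven safety, and nothing else says how that would be judged.

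A reader might also infer that the trial is likely to miss its endpoint from background events alone. The documents do not support that. It needs an any-cause rate above 6.7%, and no rate is given. Participants are outpatients, and the exclusion criteria remove significant acute illness, recent suicidal behaviour, recent malignancy, and recent or planned major surgery. The nearest figure in the protocol, 1.3% for cardiovascular events in HIV trials, is not a post-stroke any-cause rate; used anyway, it would give only 1 − 0.987^10 = 12.3%.

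Nor is counting all causes an error. It is a defensible choice, and adjudication would identify an unrelated event as such.

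The wide interval comes from n = 10 in a declared proof-of-concept study, and rewording will not narrow it. A drug with a true 20% rate would also show at least one event 89% of the time, which is not poor for a pilot screen. Both points are fair. They argue for reporting the bound, not for leaving it out.

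Finally, interval methods and extra tables often belong in the SAP. That is true of the detail. The definition of the primary endpoint and the claim made from it are protocol matters, and both are fixed here.

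**Conclusion.** The point holds as one about the definition of the endpoint and the conclusion drawn from it. Zero events in 10 cannot prove safety, because true rates up to 30.8% (two-sided 95%) or 20.6% (one-sided 90%) are not excluded. This needs only n = 10 and independent participants. One event cannot show lack of safety either: over an assumed any-cause rate of 2% to 10%, between 18% and 65% of such trials would have at least one event with a harmless drug. That range is an assumption and no figure in the protocol fixes it, so the supported statement is that a harmless drug may well miss the endpoint, not that it probably will. Estimation also fits the protocol better, since its sample size text justifies the pilot as a way to estimate tolerability and already converts zero events into bounds for three other outcomes.

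**What to change.** 1. Restate the primary safety endpoint as: *the number and proportion of participants with at least one serious TEAE or TEAE leading to discontinuation, any cause, with an exact two-sided 95% confidence interval.*
2. Beside it, show the subset that the safety committee adjudicates as treatment-related.
3. In Design, replace the condition that the drug be proved safe with wording that refers to this estimate and its upper limit.

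The cost is a change of wording and one extra table column. No additional patients, visits or data are needed, and clinical management is unaffected. The downside for the sponsor is giving up a simple statement that no events means safe, in exchange for a less favourable bound.

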**CGI-I and CGI-S** - The clinical global impression – improvement (CGI-I) is a 7 point scale that requires the [clinician](https://en.wikipedia.org/wiki/Clinician) to assess how much the patient's illness has improved or worsened relative to a baseline state at the beginning of the intervention; The clinical global impression – severity (CGI-S) evaluates the severity of psychopathology from 1 to 7, and will provide an overall clinician-determined summary measure that takes into account all available information, including knowledge of the subject’s history, psychosocial circumstances, symptoms, behavior, and the impact of the symptoms on the subject’s ability to function (Guy 1976).

**GAD-7** - The 7-item patient-reported generalized anxiety disorder 7-item scale (GAD-7) is a brief and valid measure of overall anxiety (Spitzer 2006). Each item is rated on a 4-point scale (0 to 3), with the total score range from 0-21 (higher scores indicating more anxiety).

**GDS** – Geriatric depression scale, that has been has been tested and used extensively with older populations.

**PGI-S and PGI-C** - Patient Global Impression scales are commonly used measures of symptom severity, treatment response and the efficacy of treatments. The patient global impression - severity (PGI-S) will provide an overall patient-rated summary measure that assesses the severity of the subject’s MDD. The patient global impression of change (PGI-C) will provide an overall patient-rated summary that assesses subject perception of change in their MDD since starting study treatment (Rush 2005).

.

**MoCA** - Montreal Cognitive Assessment.

**SIS** - stroke impact scale.

**ADL** - the activities of daily living score.

**RNL** - Reintegration to Normal Living Index.

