**Recruitment and retention plans**

Screening and patient evaluation:

Participants will be out-patients referred from the community or the hospital’s ambulatory services, who meet entrance and exclusion criteria. After receiving a detailed explanation and signing informed consent, the participant will be further screened. All identifying information of participants will be saved in a separate password protected study log available only to study investigators. All the gathered data will be de-identified and coded with a pre-assigned study ID.

Eligible patients enrolled in the study will undergo a baseline visit (Week 1), in which they will receive the study drug following completion of all relevant assessments. During the first administration, participants will remain under clinical supervision and vital signs monitoring for 2 h at the Tel Aviv Sourasky Medical Center. Blood pressure and heart rate will be recorded before discharge. Patients will be evaluated every 2 weeks during the trial using multiple depressive, anxiety and functional questionnaires as well as cognitive tests. A final safety and efficacy assessment will be held 8 weeks after the patient’s last dose (Week 18).

Open-label treatment period:

On Day 1, subjects will start the study drug. A 1-week supply of capsules will be handed to participants after the consent has been signed, and baseline measurements obtained, usually on the same day. The second 2-weeks supply will be provided during a scheduled interim measurement assessment at TLVMC near the end of the 2nd week on medication. Participants will take Maraviroc 300 mg at 6-8AM. The capsules will be supplied by the hospital pharmacies and used under IRB approval as required.

The efficacy, safety, and biomarker evaluations that will be performed at each visit of the treatment phase and are described in the Time and Event Schedule.

Post-treatment phase

The efficacy and safety evaluations that will be performed at each visit during the post-treatment phase are described in the Time and Event Schedule.

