All subjects who receive at least 1 dose of study medication should have 2 follow up visits conducted at 4 and 8 weeks after the last dose of study medication. The follow up visits at weeks 3, 5, 8, 9 will be telephone contacts. The follow up visit at 4 and 8 weeks after the last dose of study medication are clinic visits. Any clinically significant abnormalities persisting at the end of the study will be followed by the investigator until resolution or until a clinically stable endpoint is reached. All adverse events and special reporting situations, whether serious or non-serious, will be reported until completion of the subject's last study-related procedure (which may include contact for follow-up of safety).

TIME AND EVENTS SCHEDULE (Table S1)

| **Week 14 (4 weeks after last dose, Week 18 (8 weeks after last dose)** | **Telephone contact (week 3, 5, 8, 9)** | **week 4, week 7, week 10** | **Week 2** | **Day 1 (can be the same as screening)** | **Screening** | **Participant Assessment** |
| --- | --- | --- | --- | --- | --- | --- |
|  |  |  |  |  | **X** | Informed consent |
|  |  |  |  |  | **X** | Inclusion / Exclusion criteria |
|  |  |  |  |  | **X** | Medical history, demographics |
|  |  | **X** | **X** | **X** |  | Study Drug Administration |
|  |  |  |  |  |  | Safety Assessments |
| **X** |  | **X** | **X** | **X** | **X** | Physical examination |
|  |  | **X** | **X** | **X** | **X** | Body weight |
|  |  | **X** | **X** | **X** | **X** | Vital signs |
|  |  | **X** | **X** | **X** | **X** | 12-lead ECG |
|  |  |  |  |  | **X** | Carotid Doppler |
|  |  |  |  |  |  | Clinical Laboratory assessments |
|  |  | **X** | **X** |  | **X** | Hematology, Chemistry |
|  |  | **X** | **X** |  | **X** | Serum cytokines |
|  |  |  |  |  |  | Efficacy assessments |
| **X** |  | **X** | **X** | **X** | **X** | MADRS (7-day recall) |
| **X** |  |  |  | **X** |  | GDS |
|  |  | **X** | **X** | **X** | **X** | CGI-I + CGI-S |
| **X** |  | **X** | **X** | **X** | **X** | QIDS-SR16 |
|  |  | **X** | **X** | **X** | **X** | PGI-S |
| **X** |  | **X** | **X** | **X** | **X** | PGI-C |
| **X**  (for suspected Dementia) |  |  |  |  | **X** | GAD-7 (7-day recall) |
| **X** |  | **X (week 10)** |  |  | **X** | MoCA |
| **X** |  | **X (week 10)** |  | **X** |  | Computerized cognitive test battery (Neurotrax) |
| **X** |  |  |  | **X** |  | SIS |
| **X** |  | **X** |  | **X** |  | ADL |
| **X** |  |  |  | **X** |  | RNL |

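### CGI-I and PGI-C already rate change since treatment start, so the planned paired change-from-baseline analysis of severity does not fit them (wrong as written, minor)

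*Protocol*

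**What the plan says.** - **Endpoint list** (Protocol, Interventions, Secondary Endpoints): "Change from baseline to week 10 in severity of illness using the CGI-S and CGI-I" and "Change from baseline to week 10 in severity of illness using the PGI-S and PGI-C".
- **Scale descriptions** (Secondary Efficacy measures): CGI-I is a 7-point scale on which the clinician is "to assess how much the patient's illness has improved or worsened relative to a baseline state at the beginning of the intervention". PGI-C "assesses subject perception of change in their MDD since starting study treatment". By contrast, CGI-S "evaluates the severity of psychopathology from 1 to 7".
- **Objectives**: the severity item of the third secondary objective names only CGI-S and PGI-S.
- **Statistical Analysis, secondary outcome analyses**: a paired t-test or signed rank test is applied to the difference in scores between baseline and weeks 10 and 18. No scale is exempted.
- **Time and Events Schedule (Table S1)**: the columns run backwards in time, with Screening nearest the row label. The shared CGI row reads "X | X | X | X | CGI-I + CGI-S", which puts marks at Screening, Day 1, Week 2 and Weeks 4/7/10. The PGI-C row has the same marks plus Weeks 14/18.
- **Recruitment and retention plans**: at the baseline visit, "they will receive the study drug following completion of all relevant assessments". Ratings made at Screening and at the baseline visit therefore precede treatment. For MADRS the endpoint list also fixes baseline as Day 1 before dosing.

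**The concern.** A severity scale such as CGI-S describes a state. It has a value before treatment and another at week 10, and the difference between them is a change. CGI-I and PGI-C are already comparisons with the start of treatment. Before the first dose there is nothing to compare, so any value entered then is a convention and not a measurement. Subtracting it from the week-10 rating gives a number whose size and sign depend on that convention. That number is not a change in severity either.

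The Protocol does not say what raters should enter before dosing. At stake are two named secondary endpoints, which could be reported as improvement, as worsening, or not at all from the same patients.

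**Working it through.** The Protocol gives no power, effect size or other figure for CGI-I or PGI-C, so there is none to reproduce. The check has two parts.

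**1. The sections side by side**

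| Section | CGI-S, PGI-S | CGI-I, PGI-C |
| --- | --- | --- |
| Scale descriptions | severity state | change since treatment start |
| Objectives, severity item | named | not named |
| Endpoint list | change from baseline in severity | change from baseline in severity |
| Statistical Analysis | paired test | paired test, no exception |
| Table S1, pre-dose | marked | marked (see the limits under the objection) |

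The scale descriptions and the objectives separate the two kinds of scale. The endpoint list and the analysis rule treat them alike.

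**2. What the paired rule gives**

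Assumptions not in the documents: 1 = best, 4 = no change, 7 = worst. The Protocol states seven points for CGI-I and gives no range for PGI-C, so this illustrates CGI-I. Sample size is the planned n = 10, with two-sided alpha 0.05.

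Hypothetical week-10 ratings in an improving group: 1, 2, 2, 3, 2, 3, 4, 2, 3, 4.

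- Mean = 26/10 = 2.6.
- Sum of squared deviations = 8.40, so SD = sqrt(8.40/9) = 0.966 and SE = 0.966/sqrt(10) = 0.3055.
- With the same pre-dose entry b for everyone, the paired change is 2.6 - b and t = (2.6 - b)/0.3055 on 9 degrees of freedom.
- When all m non-zero differences have one sign, the exact signed-rank p is 2/2^m.

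| Pre-dose entry b | Mean change | t | t-test p | Signed-rank p | Would be read as |
| --- | --- | --- | --- | --- | --- |
| 4 | -1.4 | -4.58 | 0.001 | 2/2^8 = 0.008 | improvement |
| 1 | +1.6 | 5.24 | 0.0005 | 2/2^9 = 0.004 | worsening |
| 0 | +2.6 | 8.51 | 0.00001 | 2/2^10 = 0.002 | worsening |
| blank | none | none | none | none | no pairs |

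The patients are identical in every row.

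**No true change.** Week-10 ratings were simulated symmetrically about 4, with probabilities 0.02, 0.08, 0.20, 0.40, 0.20, 0.08, 0.02 for scores 1 to 7 and 5,000 runs of n = 10.

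- Testing the rating directly against 4 rejected in 4.1% of runs, close to the nominal 5%.
- Subtracting a placeholder of 0 or 1 rejected in 100% of runs, practically always towards worsening. The expected spurious change is 4 - 0 = 4 or 4 - 1 = 3 points.

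The direction depends on the assumed numbering. If higher scores meant better, the same placeholders would push towards improvement.

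**The case against.** The best defence is that the endpoint wording can be read loosely: severity of illness is what changes, and CGI-I and PGI-C are instruments for rating that change. The week-10 rating would then be the endpoint and would be well defined. This softens the endpoint list, and the objectives lend it some support. It does not reconcile the list with the analysis rule, which asks for a difference in scores from baseline and makes no exception.

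Three further points stand and limit the finding.

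- **The schedule is supporting evidence only.** CGI-I shares its row with CGI-S, which needs the pre-dose marks, so the row does not prove that CGI-I is to be rated before dosing. The PGI-C and GAD-7 rows may be misaligned. The GAD-7 row carries a note about suspected dementia that fits the MoCA row below it, and it has no week-10 mark although GAD-7 is a week-10 endpoint. The PGI-C row has the marks GAD-7 would need. Whether this lies in the source or in the text extraction cannot be settled here.
- **The harm is conditional.** If no change is entered for everyone before dosing, a natural answer on such a scale, the paired test is exactly a one-sample test against no change and is valid.
- **The codes are assumed.** The documents give neither anchors nor a code for not assessed.

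A statistical analysis plan may exist and could settle how pre-dose entries are handled. The conflict between the scale definitions and the analysis rule is nonetheless in the Protocol's own text, so it is not merely a detail left for later.

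**Conclusion.** Wrong as written, minor. The Protocol defines CGI-I and PGI-C as change ratings and then assigns them a change-from-baseline endpoint in severity and a paired baseline test. Under that rule the result depends on an unspecified pre-dose entry. Under the assumed anchors it ranges from a valid one-sample test (entry of 4), through a spurious shift towards worsening (0 or 1), to no analysis (blank).

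A reader might infer that both endpoints are undefined and bound to be artefact or empty, or that the plan would manufacture a benefit. The documents do not support this. The week-10 ratings will exist and can be summarised whatever happens before dosing, one plausible entry makes the planned test valid, and the direction of any artefact depends on codes the Protocol does not give.

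The effect is confined to two secondary scales in a 10-patient, open-label pilot whose primary objective is safety. MADRS, CGI-S, PGI-S and the safety endpoint are unaffected.

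**What to change.** 1. In the endpoint list, keep change from baseline to week 10 for CGI-S and PGI-S only, in line with the objectives.
2. Define the CGI-I and PGI-C endpoints as the week-10 rating itself. Summarise it as a distribution or as the proportion improved with an exact confidence interval. If a test is wanted, use a one-sample signed-rank test against the no-change category. State the anchors of both scales.
3. In the Statistical Analysis section, exempt these two scales from the paired baseline comparison, including at week 18 if the PGI-C mark there is confirmed.
4. In Table S1, first check the PGI-C and GAD-7 rows against the source for misalignment. Then split the CGI row and remove the Screening and Day 1 marks for CGI-I and PGI-C.

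The cost is a few lines of wording, one row split and four schedule positions (two visits for two scales). No visit, patient or assessment is added.

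### Table S1 schedules no week-10 SIS or RNL, and apparently no week-10 GAD-7, although the endpoint list defines all three as change from baseline to week 10

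*Protocol*

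**What the plan says.** The endpoint list (Protocol, Interventions, Secondary Endpoints) gives "Change from baseline to week 10 in anxiety symptoms, as measured by the GAD-7" and "Change from baseline to week 10 in the SIS, ADL, and RNL scores". The Efficacy Assessments part of Statistical Analysis plans paired tests of functional scores from baseline to weeks 10 and 18. Treatment is "an open-label treatment phase of 10 weeks" (Overview of Study Design), so week 10 is the end of treatment and weeks 14 and 18 are off drug.

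The schedule is Table S1. Its columns run backwards in time, from weeks 14/18 on the left to screening on the right. The row labelled "GAD-7 (7-day recall" is marked at screening and at weeks 14/18, and the later mark carries the note "for suspected Dementia". SIS and RNL are marked on Day 1 and at weeks 14/18. ADL, printed between them, is also marked in the weeks 4/7/10 column.

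Under Recruitment and retention plans, the evaluations at each treatment visit "are described in the Time and Event Schedule". The same section also says that patients are assessed at two-week intervals with depression, anxiety and functional questionnaires. Supplementary Figure S1 and the follow-up paragraph after Table S1 list questionnaires at week 10 without saying which.

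**The concern.** An endpoint defined as change to week 10 needs a week-10 measurement. If the schedule does not call for one, staff working from it will not collect it, and a missed questionnaire cannot be recovered once the patient has passed that visit. Anxiety and functional outcome are both stated secondary objectives, and with 10 patients planned there is little room for gaps. A statistical analysis plan could not repair this, because it can only analyse what the visit schedule collects.

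**Working it through.** No sample-size or power figure bears on this point. The check maps each Table S1 row to its column headings and compares it with the endpoint list.

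**1. Rows as printed**

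| Instrument | Endpoint time point | Screening | Day 1 | Week 2 | Weeks 4/7/10 | Weeks 14/18 |
|---|---|---|---|---|---|---|
| GAD-7 | Week 10 | X | – | – | – | X (with note) |
| SIS | Week 10 | – | X | – | – | X |
| ADL | Week 10 | – | X | – | X | X |
| RNL | Week 10 | – | X | – | – | X |

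**2. Count.** The clinic visits on treatment after Day 1 are weeks 2, 4, 7 and 10, which is four visits. Scheduled assessments at those visits are GAD-7 0, SIS 0, RNL 0 and ADL 3. At week 10 alone they are 0, 0, 0 and 1. So 3 of the 4 instruments cannot yield a week-10 change under the table. Their first scheduled value after baseline is at week 14, which is 14 − 10 = 4 weeks after the last dose.

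**3. Is the empty cell an artefact of the column?** No. The weeks 4/7/10 column is in use: ADL has a plain mark there, and MoCA and the computerized battery have marks restricted to week 10. Reading the columns in the opposite order gives no week-10 mark for GAD-7, SIS or RNL either.

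**4. Could the rows have slipped?** The dementia note fits a cognitive test better than an anxiety scale, and MoCA is the next row down. Two versions of a slip can be tried:
- *Slip limited to the GAD-7 and MoCA rows.* GAD-7 would take the PGI-C marks and gain week 10. SIS and RNL would be unchanged, so 2 of 4 instruments would still lack week 10.
- *All marks belong one row lower.* GAD-7 takes the PGI-C marks, SIS takes those of the computerized battery and RNL takes those of ADL, so all three gain week 10. ADL then takes the SIS marks and loses it, so 1 of 4 lacks week 10.

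On each of these readings, at least one instrument in the SIS/ADL/RNL endpoint has no week-10 assessment.

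**5. Does the general text settle it?** The two-weekly sentence names no instrument. Two-week spacing also does not match clinic visits at weeks 2, 4, 7 and 10, where the gaps are 2, 3 and 3 weeks. The section containing that sentence refers to the schedule for the content of each treatment visit.

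**The case against.** The strongest reply is that the protocol does intend these data to be collected. GAD-7 is its only anxiety scale, and the objectives class SIS, ADL and RNL as functional outcomes. A two-weekly round of anxiety and functional questionnaires would therefore cover them in effect. Figure S1 and the follow-up paragraph place questionnaires at week 10, and the analysis section expects functional scores then. The visit-window footnote to Table S1 (Days 15, 29, 43, 57 and 71) also has two-week spacing, so the sentence does not stand alone.

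Part of this stands. The problem is a conflict between text and table, and the intention to measure at week 10 is fairly clear. A reader might infer that none of the 10 patients would have a week-10 value. The documents support that only if the table is followed over the general text. Still, the general text does not cure the conflict: it names no instrument, its timing does not fit the visit columns, and the protocol makes the table the description of visit content.

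The doubt about the GAD-7 row also stands. A reader might take the note literally and conclude that patients without suspected dementia have no GAD-7 after baseline. That does not hold together with the view that the note is in the wrong row, which is the more plausible explanation. SIS and RNL are firmer, because they contrast directly with the ADL row between them.

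**Conclusion.** The contradiction is real. As printed, Table S1 provides no on-treatment SIS, RNL or GAD-7 after Day 1, while the endpoint list requires week-10 values for all three and the analysis section tests functional scores at week 10. Confidence is high for SIS and RNL and lower for GAD-7. ADL is unaffected as printed. The practical consequence assumes that sites take visit content from Table S1, as the protocol tells them to.

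This is a should-fix item. It concerns secondary endpoints in a 10-patient open-label trial whose primary objective is safety, and MADRS is scheduled in the weeks 4/7/10 column.

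Three stronger inferences are not supported:
- *The dementia note contradicts the exclusion of dementia.* That exclusion applies at screening, so a suspicion arising by week 14 or 18 would not conflict with it.
- *GDS has the same defect.* GDS has no week-10 mark, but it is not in the endpoint list, and the analysis section does not name it.
- *Off-drug week-14 values would be reported as the treatment result.* No passage proposes that substitution, and the analysis section gives week 18 its own comparison.

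**What to change.** In Table S1, add a week-10 mark for SIS, RNL and GAD-7, and keep the existing ADL mark. Move the dementia note to the row it belongs to, after checking the marks in the neighbouring rows against the source table. Reword the two-weekly sentence under Recruitment and retention plans so that it matches the scheduled visits, and bring the visit-window footnote into line. It would also help to name the week-10 instruments in the follow-up paragraph.

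The cost is a table correction by amendment and three questionnaires at a clinic visit that already takes place. Redefining these endpoints at weeks 14/18 and labelling them post-treatment would also remove the contradiction, but it would leave no end-of-treatment measure of anxiety, stroke impact or reintegration.
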